### Health risk appraisal (HRA) questionnaire

The HRA is comprised of demographic, health and lifestyle factors, as well as questions related to stages of change for the various risk behaviours. The demographic variables include age and gender; while the lifestyle measures include, fruit and vegetable intake, habitual alcohol consumption and habitual physical activity. For smoking, fruit and vegetable intake and habitual physical activity, the participant also reports on readiness to change or improve these behaviours. The questions on readiness to change are based on the Transtheoretical Model stages of change [6]. Additionally, the health screening will be comprised of the finger-prick capillary blood samples for serum cholesterol and glucose concentrations, blood pressure, height and weight measurements. All screening will conducted by qualified, trained staff, provided by the health insurer and will form part of their wellness day which is offered to their corporate clients.

### Habitual physical activity

Habitual physical activity will be measured using the ‘Global Physical Activity Questionnaire’ (GPAQ) [31]. This is a self administered questionnaire that includes questions on habitual levels of light, moderate and vigorous activity. The physical activity domains include work-related activity, transport and leisure time activity, which are then summed to calculate total minutes of physical activity per week. Participants will be categorised according to whether they meet the American College of Sports Medicine guideline of 150 minutes of physical activity per week.

#### Dietary habits

Habitual dietary fat intake will be measured using the Short Fat Questionnaire [32]. The data obtained from this questionnaire will supplement the information on habitual fruit and vegetable intake and general dietary habits obtained from the Health Risk appraisal.

#### Presenteeism and absenteeism

The Healthy Days Questionnaire devised and tested by the US Centers for Disease Control and Prevention, will be used to measure health-related quality of life. Healthy days are calculated using a series of 4 questions, focusing on general perceived health, self-rated physical and mental health and the extent to which physical and/or mental health may have limited work-related activity within the past 30 days [33]. Absenteeism data will be obtained from the company’s Human Resource office, in addition to the participant keeping a log book so that the wellness specialist can record days away from work at each consultation and at the 6 and 12 month follow up visits.

#### Clinical measures

The following clinical measures will be performed by the trained health professionals employed by the health insurer at the wellness days. Cholesterol screening will be conducted using finger-prick capillary blood samples (Accutrend ® GC analysers, Roche Diagnostics) to measure total serum cholesterol concentrations. Systolic and Blood pressure will be measured twice per person using an automated sphygmomanometer. Employees will be instructed to sit quietly for approximately three minutes before being measured. Both readings will be recorded and the average of the two will be used in the statistical analysis.

Standing height (cm) will be measured to the nearest 0.1 cm, using a stadiometer. Body weight will be measured using a portable calibrated scale and recorded to the nearest 0.1 kg. Employees will be asked to remove shoes, jackets/jumpers/jerseys and asked to empty pockets for these measurements. Body Mass Index (BMI) will be calculated as body mass (kg) divided by height (m) squared (kg/m2).

### Process measures

A process evaluation will be conducted to determine if the intervention was implemented as intended. The counsellors and participants will be asked to critically appraise the various components of the intervention and to grade their experience. This appraisal will include a selfreport on the frequency and ease of use of the key concepts and tools applied during the motivation interviewing session, such as the importance and confidence rulers. Counsellors will also record the number of telephone calls and emails sent prior to confirming an appointment with the employee, the number of missed and re-scheduled appointments and additional information that may be requested by the employee.

A sub-sample of participants will be contacted post the intervention and invited to a focus group discussion to relay their experiences and assessment of the counselling sessions. Fidelity and adherence to the motivational interviewing technique will be measured by the principle researcher, using the ‘Motivational Interviewing Treatment Integrity (MITI) scoring methodology which incorporates the random recording and evaluation of their audio recorded counselling sessions.

#### Costs

The intervention costs that will be included are the cost of the wellness days screening, training of counsellors, employment costs of counsellors, opportunity cost that may be lost if employee’s sessions are during working hours, health promotion materials, travel and telephone calls. These data will be obtained from the health insurer who will keep records of all expenses related to the intervention, which includes the duration of counselling sessions.

Direct health care costs will be based on health-related claims data linked to doctors visits, hospitalisation and chronic medication will be obtained from the medical insurer. Indirect costs include costs for loss of productivity (i.e. sickness absenteeism). Absenteeism data will be obtained from the company Human Resource manager in each company. In addition, participants will keep a medical costs and absenteeism diary and submit it to the research team every 3 months.

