### Intervention group

The wellness specialists will calculate the adapted Framingham score for all employees who have voluntarily participated in their worksite’s wellness day. All employees who are identified as being at increased risk will receive a telephone call from the wellness specialist inviting them to participate in the research study. Should they agree, the wellness specialist will book the first face-to-face session, which will take place at the employee’s worksite.

Individuals in the intervention group will receive the same advice and health promotion materials as those in the control group. Additionally, they will be offered an individually tailored intervention that consists of one-on-one counselling sessions. The first intervention group will receive the six one-on-one counselling sessions over a 6-month period (6-I), while the second intervention group will receive the counselling over a 3-month period (3-I).

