### Control group

The employees in the control group will receive usual care. This is comprised of feedback at the health and wellness day, directing employees to their physician if needed, and encouragingthem to increase their level of physical activity and to improve nutrition in a generic way. They will receive general health promotion material detailing the risks for cardiovascular disease and once-off advice on improving lifestyle behaviour. The participants from the control companies will also participate in follow up measurements at 6 and 12 months.

If the intervention is shown to be effective, the companies who were in the control group will receive the intervention after completion of the research study. Therefore, the control group will be wait-listed for the intervention.

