### Statistical analyses

STATISTICA software package will be used for all the analyses (Stasoft, Inc. 184–199, Tulsa OK, SA) and intention to treat analysis will be performed for each of the outcomes. Mean, standard deviation and standard error will be calculated for the continuous variables. Frequency tables will be used to determine the percentage of individuals at risk. An Analysis of Variance (ANOVA) will be performed to determine whether there were significant changes in physical activity habits and nutrition in the intervention and control groups at 6 and 12 months.

The cost-effectiveness of the intervention programme will be determined from the societal and the employer perspective. Confidence intervals around differences in costs between the intervention groups and control group will be estimated using bootstrapping techniques. Cost effectiveness ratios will be calculated by dividing the difference between the mean total costs of the intervention groups and control group, by the difference in the mean habitual physical activity levels and total number of risk factors for cardiovascular disease. Uncertainty around the cost-effectiveness ratios will be graphically presented on Cost-Effectiveness planes (CE-planes) [34]. Furthermore, Cost-effectiveness acceptability curves will be estimated to show the probability of cost-effectiveness at different ceiling ratios [35].

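### Screening and general health promotion materials that both arms receive are listed as intervention costs with no matching control cost; charged to one arm only, they inflate the cost difference by their per-head cost

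*Protocol article*

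**What the plan says.** The Costs section names three groups of cost: intervention costs, direct health care costs from claims, and indirect costs from absenteeism. The first group begins: "The intervention costs that will be included are the cost of the wellness days screening, training of counsellors". It goes on to counsellor employment and employee time, and ends with "health promotion materials, travel and telephone calls". The stated source is the insurer's records of expenses related to the intervention.

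The Control group section describes usual care: "This is comprised of feedback at the health and wellness day, directing employees to their physician if needed". It adds: "They will receive general health promotion material detailing the risks for cardiovascular disease". The same section has control participants attend the 6- and 12-month measurements.

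The Intervention group section says: "Individuals in the intervention group will receive the same advice and health promotion materials as those in the control group". It then states what is extra: "Additionally, they will be offered an individually tailored intervention that consists of one-on-one counselling sessions".

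According to Study population, all employees of eligible companies are invited to the wellness day, and the insurer offers and conducts the assessment there. The Health risk appraisal section describes the screening as part of a service that the insurer offers its corporate clients.

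Under Statistical analyses, the cost-effectiveness ratio is obtained by "dividing the difference between the mean total costs of the intervention groups and control group" by the difference in mean physical activity and in the total number of risk factors. The perspectives are societal and employer.

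**The concern.** An incremental analysis against usual care should charge the intervention arm only with what it receives beyond usual care. Anything that both arms receive should cancel. Here two items that controls also receive are classed as intervention costs, and none of the three cost groups holds a corresponding programme cost for controls. An analyst who follows the list literally, using records kept for the intervention, would charge the shared items to one arm.

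That would move the cost difference against the intervention, and the cost-effectiveness planes and acceptability curves with it. A true net saving could be reported as smaller than it is, or as none. The economic evaluation is a declared aim in the Background, and the abstract presents it as important to health care funders.

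**Working it through.** **Step 1: which listed items are shared.**

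| Item in the Costs list | Does the control arm receive it? | Source |
|---|---|---|
| Wellness-day screening | Yes | Study population; Control group |
| Health promotion materials | Yes for general materials; materials specific to counselling may exist | Control group; Intervention group; Step 3 |
| Counsellor training and employment | No | Intervention group |
| Employee time in sessions | No | Intervention group |
| Travel and telephone calls | Not listed as part of usual care | Costs; Control group |

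The article states no unit cost, incremental cost or ratio, so there is no figure of its own to reproduce. The check is algebra on its definition of the ratio.

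**Step 2: the algebra.** Let

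- S = per-head cost of the shared screening and general materials
- M = per-head cost of the counselling alone
- O = between-arm difference in claims and absenteeism costs (intervention minus control)
- E = between-arm difference in effect

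Shared items in both totals: cost difference = (S + M + O) − S = M + O, and ratio = (M + O)/E.

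Shared items in neither total: cost difference = M + O, the same result.

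Shared items in the intervention total only: cost difference = S + M + O, and ratio = (S + M + O)/E.

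The error in the cost difference is therefore exactly S, and the error in the ratio is S/E.

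**Step 3: illustration.** All values are assumptions in arbitrary currency and none comes from the article: M = 1000, E = 30 minutes per week, and S from 50 to 500.

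| O | Correct difference (ratio) | One-sided, S = 50 | One-sided, S = 200 | One-sided, S = 500 |
|---|---|---|---|---|
| 0 | 1000 (33.3) | 1050 (35.0) | 1200 (40.0) | 1500 (50.0) |
| −900 | 100 (3.3) | 150 (5.0) | 300 (10.0) | 600 (20.0) |
| −1500 | −500 (−16.7) | −450 (−15.0) | −300 (−10.0) | 0 (0.0) |

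For a given S the absolute error is the same in every row: 50/30 = 1.7, 200/30 = 6.7 and 500/30 = 16.7 per minute per week. The relative error is S/(M + O), so it depends on the claims and absenteeism difference as well as on the counselling cost. It is largest when savings nearly offset the counselling cost. In the last row, one-sided charging with S = 500 removes the saving altogether.

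**The case against.** The strongest reply is that a list of categories is not an allocation rule. The ratio uses mean total costs in each arm. If screening and shared materials are also charged to controls, they cancel and nothing is wrong. A condensed article may also leave item-by-arm costing to a fuller economic plan that is not shown. This stands in part. It means that a reader who infers that the incremental cost is certainly overstated goes beyond the text, which does not settle the matter. It does not clear the list. The article does not leave the components open: it enumerates them, and it labels as intervention cost two items that its own arm descriptions make common to both arms.

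A reader might also infer that every ratio is inflated. The article does not support that, for three reasons.

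- The insurer conducts the screening and the article does not say who pays, so screening may not enter the employer perspective at all.
- The shift S/E is upward only when E is positive. One denominator is the number of risk factors, where benefit is a reduction, and no sign convention is given.
- Step 3 speaks of materials matched to the individual's needs, so part of the materials line may belong to counselling.

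Finally, it is tempting to express the error as a percentage of the counselling cost, or to load the whole screening bill onto those who enrol. The first ignores claims and absenteeism costs in the numerator. The second assumes an allocation that the article nowhere describes.

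**Conclusion.** The concern holds in conditional form. The cost list conflicts with the definition of the comparator, because it classes screening and general materials received by both arms as intervention costs and names no matching control cost. Applied as written to the intervention arm only, it makes the cost difference too high by S and shifts each ratio whose perspective includes these items by S/E. With the items in the list, the bias is zero only if controls are charged the same amount, which the article does not say.

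The size cannot be determined from the article. The conclusion assumes that the per-head cost of the shared items is the same in both arms and that S covers only general materials. It bears on the economic evaluation alone; the primary comparison of physical activity is untouched. The change is worth making before costs are analysed.

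**What to change.** In the Costs section, define intervention costs as the increment over usual care: counsellor training and employment, employee time in sessions, travel, calls, and any materials given only at counselling. State that wellness-day screening (baseline and follow-up) and general health promotion materials are left out of both arms or, where records allow, costed identically in both. If funders want screening plus counselling compared with nothing, report that as a separately labelled scenario.

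This is a change of a sentence or two. Leaving the shared items out of both arms needs no new data. Costing them in both may need expense records for control companies, which the article does not mention: the records it describes are those related to the intervention.

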### Statistical analyses

STATISTICA software package will be used for all the analyses (Stasoft, Inc. 184–199, Tulsa OK, SA) and intention to treat analysis will be performed for each of the outcomes. Mean, standard deviation and standard error will be calculated for the continuous variables. Frequency tables will be used to determine the percentage of individuals at risk. An Analysis of Variance (ANOVA) will be performed to determine whether there were significant changes in physical activity habits and nutrition in the intervention and control groups at 6 and 12 months.

The cost-effectiveness of the intervention programme will be determined from the societal and the employer perspective. Confidence intervals around differences in costs between the intervention groups and control group will be estimated using bootstrapping techniques. Cost effectiveness ratios will be calculated by dividing the difference between the mean total costs of the intervention groups and control group, by the difference in the mean habitual physical activity levels and total number of risk factors for cardiovascular disease. Uncertainty around the cost-effectiveness ratios will be graphically presented on Cost-Effectiveness planes (CE-planes) [34]. Furthermore, Cost-effectiveness acceptability curves will be estimated to show the probability of cost-effectiveness at different ceiling ratios [35].

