### Step 5: Adoption and implementation plan

#### Pilot study

A pilot study was conducted in a convenient sample of employees for 12 weeks. The aim of the pilot was to determine the feasibility of the interventions and also to allow the counsellors to gain experience and proficiency in motivational interviewing techniques.

Eight wellness counsellors, based in three different South cities, recruited a convenience sample of both male and female employees (n = 225). The baseline participant characteristics are presented in Table 2. Despite the mean serum cholesterol and blood pressure being within normal ranges, more that 80% of the employees volunteering to participate had two or more risk factors for cardiovascular disease.

**Table 2 T2:** Baseline characteristics of participants in the pilot study

	**n**	**Mean**	**± Standard Deviation**
Age (years)	225	40.0	10.8
Men (% of total sample)	121	51%	
Body Mass Index (kg/ht2)	225	31.0	5.5
Cholesterol (mmol/l)	228	4.7	0.9
Diastolic Blood Pressure (mm Hg)	229	84.1	11.6
Physical Activity (min/wk)	225	63.0	120.9

The analysis of covariance (ANCOVA) was performed to measure the effectiveness of the 12-week intervention. Participants were grouped into being either at risk or not at risk for each of the individual risk factors, and then the baseline and follow up measures were compared for each specific risk factor. Diastolic blood pressure decreased significantly over the 12 weeks period among those whose baseline result placed them in the at risk group (Diastolic blood pressure more than 90 mmHg) from 95.8 mmHg ± 9.8 to 90.1 mmHg ± 13.7 (p < 0.0001). Similarly, those with 2 or more risk factors at baseline decreased their number of risk factors from 3.5 ±0.8 to 3.0 ± 1.0 at follow up (p < 0.0001). In addition, there was a significant group and time effect for Body Mass Index, where those who were overweight or obese (BMI >25) at baseline experiencing a slight decline at 12 weeks (data not shown). This is an encouraging finding as 83% of the participants were either overweight or obese at baseline.

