#### Sample size calculation

The sample size was determined according to a power calculation using a dichotomous variable: meeting the PA guideline with at baseline 50% not meeting the guideline and after the intervention 40% (intervention group) vs 50% (in control group). Based on these numbers, and 80% power and significance of 0.05, 775 employees are required at the 12-month follow-up with 387 in control group and 387 in intervention group. Thus, assuming that approximately 20% of participants will be lost to follow-up at 12 months, we will aim to recruit 928 employees at baseline and allocate 424 to the intervention and control groups (Figure 1).

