### Outcome measures

The primary outcome of this study is a change in level of habitual daily physical activity. Secondary outcomes include: changes in dietary intake and Body Mass Index. Further, the secondary outcome measures include changes in the cardiovascular disease risk profile, which will be defined by the adapted Framingham score, incorporating blood pressure, total blood cholesterol, and smoking status. Data will be collected at baseline and at 6 and 12 months.

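### The only test named for physical activity is an ANOVA of changes with no baseline covariate; a follow-up comparison adjusted for baseline and for company would generally use the data better

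*Protocol article*

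**What the plan says.** The Outcome measures section of the protocol article defines the endpoint: "The primary outcome of this study is a change in level of habitual daily physical activity". The same section gives the schedule: "Data will be collected at baseline and at 6 and 12 months".

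Statistical analyses names a single model: "An Analysis of Variance (ANOVA) will be performed to determine whether there were significant changes in physical activity habits and nutrition". The test covers both arms and both follow-up visits. The Methods part of the Abstract names the same technique for physical activity. Neither place mentions a baseline covariate or gives a reason for omitting one.

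The article mentions covariance analysis once, for the pilot: "The analysis of covariance (ANCOVA) was performed to measure the effectiveness of the 12-week intervention".

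The sample size rests on a different form of the endpoint. Under Sample size calculation: "The sample size was determined according to a power calculation using a dichotomous variable", namely whether the activity guideline is met, with "after the intervention 40% (intervention group) vs 50% (in control group") not meeting it. The section then sets the total: "Based on these numbers, and 80% power and significance of 0.05, 775 employees are required at the 12-month follow-up". That total is split equally, 387 to each arm. The Randomisation section allocates whole companies.

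**The concern.** Every participant should have a baseline value of the primary measure, because baseline is the wellness-day screening that precedes invitation. How that value enters the analysis affects two things.

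- **Precision.** The efficient weight for baseline is the regression slope of follow-up on baseline. An ANOVA fixes the weight in advance, at 1 for changes or 0 for follow-up values. Either choice generally wastes information that the trial already holds.
- **Chance imbalance.** Companies are randomised, and activity is self-reported and very variable (pilot mean 63.0, SD 120.9 min/week), so the arms may start apart. A change score subtracts the whole gap although only part of it would persist. The arm that starts less active then tends to show the larger rise through regression to the mean. A follow-up comparison ignores the gap and errs the other way.

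The wording does not settle which ANOVA is meant, so it needs a clarifying edit in any case. Nutrition is to be tested by the same method and is affected in the same way.

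**Working it through.** **1. Reproduce the plan's figure.** Inputs from Sample size calculation: 50% v 40%, 80% power, significance 0.05 (taken as two-sided). The pooled formula is n = [1.96·√(2·0.45·0.55) + 0.8416·√(0.25 + 0.24)]² / 0.10² = 387.3 per group, or 774.7 in total. This matches the stated 387 and 775. Power at 387 per group is 79.97%. The calculation treats employees as independent.

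**2. Put the three analyses on one scale.** The standardised difference with 80% power at 387 per group is d = 2.8016·√(2/387) = 0.2014. With ρ the baseline-to-follow-up correlation (assumed, since the article gives none), the variance multipliers v are 1 for follow-up ANOVA, 2(1−ρ) for change-score ANOVA and 1−ρ² for ANCOVA. Power = Φ(2.8016/√v − 1.96).

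| ρ | Follow-up ANOVA | Change ANOVA | ANCOVA | Gain over follow-up | Gain over change |
|---|---|---|---|---|---|
| 0.3 | 80.0% | 65.8% | 83.6% | 3.6 | 17.7 |
| 0.5 | 80.0% | 80.0% | 89.9% | 9.9 | 9.9 |
| 0.7 | 80.0% | 95.1% | 97.5% | 17.5 | 2.4 |

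At ρ = 0.5 the two ANOVAs coincide because 2(1−0.5) = 1. For the guideline dichotomy (50% v 40%, 387 per group, 4,000 simulated trials per correlation), power was 79.9% unadjusted and 89.6% adjusted at a correlation of 0.5, and 79.5% and 84.2% at 0.3.

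**3. Effect of an imbalance, independent employees.** A baseline gap D shifts the change-score contrast by −(1−ρ)D and the follow-up contrast by +ρD. With the pilot SD, the standard error of the gap is 120.9·√(2/387) = 8.7 min/week. A gap of one standard error at ρ = 0.5 shifts either contrast by 8.7 × 0.5 ≈ 4.3 min/week. The detectable difference is 0.2014 × 120.9 ≈ 24.3 min/week.

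**4. Company randomisation.** The article gives no intraclass correlation (ICC) and no number of companies. Assume 8 companies per arm with 48 employees each, ICC 0.05 and overall ρ 0.5. Let r_B be the correlation of company-level values over time, and r_W = (0.5 − 0.05·r_B)/0.95 the within-company correlation. If baseline has weight b, the variance of the treatment contrast in SD units is (2/8)·[0.05(1 + b² − 2b·r_B) + 0.95(1 + b² − 2b·r_W)/48]. Setting b = 0, 1 and about 0.5 gives these standard deviations:

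| r_B | Follow-up (b = 0) | Change (b = 1) | ANCOVA (b ≈ 0.5) |
|---|---|---|---|
| 0.6 | 0.132 | 0.123 | 0.109 |
| 0.8 | 0.132 | 0.100 | 0.097 |
| 0.95 | 0.132 | 0.080 | 0.087 |

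Simulation under the same assumptions agrees (change v ANCOVA: 0.124 v 0.109, 0.098 v 0.097, 0.080 v 0.087). ANCOVA beats the follow-up comparison throughout. Its advantage over the change score is clear at 0.6, nearly gone at 0.8 and reversed at 0.95.

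**5. Why company must be in the model.** Without a company term, the model-based standard error of ANCOVA at ρ = 0.5 is √(0.75·2/384) = 0.0625, against true values of 0.087 to 0.109. A nominal 5% test then rejects a true null with probability 2·[1 − Φ(1.96 × 0.0625/0.087)] ≈ 16%, up to about 26% at 0.109.

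**The case against.** Several objections carry weight.

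- **Baseline differences left uncorrected.** A reader might infer that the plan makes no correction for baseline. The article does not support that. The endpoint is a change and the ANOVA is of changes, so the natural reading is a change-score or group-by-time analysis, which subtracts baseline. Under randomisation it is also unbiased on average. What remains is over-correction conditional on an imbalance. Only an ANOVA of follow-up values would leave the gap untouched.
- **A flat loss of ten points.** A reader might also take about 10 points as this trial's loss. It is not. The correlation of 0.5 is assumed, and the 80% starting point belongs to a dichotomous outcome in independent employees. Only the range, labelled as illustrative, can stand.
- **The pilot.** It is tempting to say that the team dropped an adjustment it had used before. The article does not name the pilot's covariate. The pilot had no control group and compared at-risk with not-at-risk employees. It shows familiarity with the technique and no more.
- **Covariates may be in an unseen plan.** This is fair as far as a covariate list goes. But the article is not silent: it names a specific method in two places, and the point concerns that method.
- **Clustering.** A company-level gap follows the company-level correlation. At r_B = 0.8 in step 4, follow-up tracks the baseline gap with slope (0.05·0.8 + 0.46/48)/(0.05 + 0.95/48) = 0.71. Individual-baseline ANCOVA then under-corrects by 0.21 per unit of gap, while the change score over-corrects by 0.29. So ANCOVA on the individual baseline does not fully remove a company imbalance. This stands, and it shapes the fix.

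**Conclusion.** The point holds as a modest, worthwhile improvement to a stated method. The named ANOVA gives baseline a weight of 1 or 0, depending on the reading, and neither is generally efficient. For independent employees at 387 per group, from a nominal 80% for an unadjusted follow-up comparison, baseline adjustment gains about 4 to 18 points over follow-up ANOVA and about 18 to 2 points over change-score ANOVA as the assumed correlation rises from 0.3 to 0.7. With companies randomised, the advantage over follow-up ANOVA persisted in every scenario examined. The advantage over a change score depends on how stable company differences are, and it reversed at an assumed company-level correlation of 0.95. The conclusion therefore rests on a correlation and a cluster structure that the article does not give. The recommendation holds only for a model that also accounts for company.

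**What to change.** In Statistical analyses, and in the Methods part of the Abstract, replace the ANOVA of changes with a between-group comparison of follow-up physical activity at 6 and 12 months. Include each participant's baseline physical activity as a covariate and account for company, for example with a random company effect. Optionally add the company mean of baseline activity, so that between-company and within-company differences can carry different weights. Use the same model for nutrition, with its own baseline. If the gain in power is quoted, give it as a range over the assumed correlation.

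The cost is a sentence of wording in each place and slightly more modelling. No new data, visits or participants are needed. Missing baseline values need a simple rule, and few are expected because the baseline screening comes before entry.
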